### Outcome measures

This study will evaluate both effectiveness outcomes (measures of impact) and implementation outcomes (measures of process). The effectiveness outcomes are system utilization measures and patient outcome measures [52–54]. Implementation outcomes include the reach of the interventions, acceptability, appropriateness, fidelity, and cost-effectiveness (Table 1).

**Table 1 Tab1:** Outcome measures

Outcome measure	Instrument	Description	Reference (instrument)
*Effectiveness outcomes*			
30-day and annual readmission rates and annual emergency services utilization	Administrative data	The number and proportion of patients readmitted into acute care units within 30-days and 365 days of last discharge.	-
Psychological wellbeing	The Clinical Outcomes in Routine Evaluation - 10 (CORE-10)	A 10- item instrument developed to monitor clinically significant change in outpatients. The CORE-10 covers four domains: Well-being, problems/symptoms, functioning, and risk, and sums up in two total scores: the mean of all items, and the mean of all non-risk items. These measures will be assessed at baseline, six and 12 months for each participant.	Skre et al. 2013 [52]
Quality of life	The 5-level EQ-5D version (EQ-5D-5L)	The EQ-5D-5L comprises of 2 sections: the EQ-5D descriptive system and the EQ visual analogue scale (EQ VAS). The descriptive system consists of five components: mobility, self-care, usual activities, pain/discomfort and anxiety/depression. Each component has 5 levels: no problems, slight problems, moderate problems, severe problems and extreme problems. The EQ VAS can be used as a quantitative measure of health outcome ranging from worst imaginable health to best imaginable health, reflecting the patient’s own judgement. These measures will be assessed at baseline, six and 12 months for each participant.	Herdman et al. 2011 [53]
Patient’s recovery	Recovery Assessment Scale (RAS)	The Recovery Assessment Scale (RAS) is a 20-item measure developed based on a process model of recovery. The RAS evaluates various aspects of recovery with a special focus on hope and self-determination. These measures will be assessed at baseline, six and 12 months for each participant	Giffort et al. 2000 [54]
Patient’s resilience	The Brief Resilience Scale	The Brief Resilience Scale evaluates the perceived ability to bounce back or recover from stress. These measures will be assessed at baseline, six and 12 months for each participant.	Smith et al. 2008 [55]
Client satisfaction/Experience surveys.	Instrument developed and pilot tested, and published by the authors	Evaluates clients’ satisfaction and experiences with supportive text messaging programs. These measures will be assessed at 12 months for each participant.	Shalaby et al. 2022 [56]
*Implementation outcomes*			
Reach	Administrative data	The proportion of target population who receive the daily supportive/reminder text message and peer support interventions across Alberta.	-
Acceptability	Instrument developed and pilot tested, and published by the authors	Evaluates clients’ satisfaction and experiences with supportive text messaging programs. These measures will be assessed at 12 months for each participant.	Shalaby et al. 2022 [56]
Appropriateness of the messages and peer support services	Sociocultural sensitivity, Gender sensitivity, Age sensitivity.	Qualitative in-depth interviews.	-
Fidelity	Administrative data	Percentage of scheduled peer support follow-up visits completed as planned. Adherence to the peer support guidelines These measures will be assessed at baseline, six and 12 months.	-
Incremental cost-utility of implementing both interventions	Administrative data	The incremental cost-effectiveness ratio (ICER) is the ratio between the difference in costs and the difference in benefits of two interventions. These measures will be assessed at baseline and 12 months.	

### Data analysis

We will conduct preliminary analysis at the end of Q2 (see Fig. 1) and continue to monitor clinical and economic results at each six-month period over years 1-3, culminating in final analysis at the end of Q2 year 3. Primary outcome measurements will be extracted from administrative data, and distribution of primary outcomes data across unexposed observation periods will be compared with the exposed observation periods. Characteristics of individuals/clusters will be summarized by exposure status to allow consideration of selection biases and lack of balance [42].

Using data from the first preliminary data analysis at the end of Q2 and refining this at each subsequent analysis, we will perform conventional regression methods to predict characteristics and risk factors for patients usually readmitted for inpatient psychiatric treatment within 30 days of discharge. We will further perform machine-learning analysis to predict individuals who may be at risk of readmission within 30 days of discharge at each step. After the first cluster is followed-up, at each step of the stepped-wedge process, we will train a machine-learning model based on existing clusters and test the accuracy of their predictions in the next cluster being followed-up. The potential predictors (features) will include all demographic variables (e.g., age, sex, gender, employment, relationships and housing status, education) and clinical/administrative variables (e.g., diagnosis, substance misuse co-diagnosis, mental and physical comorbidities, presentations to the ED or utilization of crisis services over the period, number of readmissions in the previous year, types of psychotropic medications patient is taking, depot injection or not, Community Treatment Order or not, whether the individual has a General Practitioner or not, and has significant family support or not). The candidate machine learning algorithms will include commonly-used regularized logistic regression based on ElasticNet [55], support vector machines (SVM) and random forest [56, 57]. We will perform feature-, model- and parameter-selection within the training data. The machine learning model could be used for future predictions of readmission but will only be validated in this project and will not be used to intervene the stepped-wedge approach, so that the internal validity and random sampling will be maintained. We hope by the end of the project, we will develop a machine learning model to differentially support individuals at risk of 30-day readmission within 30 days of their discharge with peer support.

Cost-utility evaluation will estimate expected incremental cost per Quality Adjusted Life Year (QALY) gained by implementing the peer support and Text4Support programs, within the Net Benefit Regression framework [58]. Differences in relevant participant cohort characteristics will be controlled for during analysis. A health system perspective and within-study analysis (only study cohort costs and outcomes) will be adopted in the evaluation, comparing resource use and health outcomes (health-related quality of life) for intervention and usual care cohorts. These will be combined to calculate within-study expected QALY for each cohort. The economic evaluation methods (e.g., discount rate choice and uncertainty characterization) will align with recent reference case recommendations [59].

To examine the mechanisms that relate the outcomes to the potential predictors, and to generate contextualized information about processes related to the proposed solution (i.e., the intervention), we will embed a one-phase qualitative component using qualitative descriptive methodology [60]. In this embedded experimental mixed methods design (also referred to as a concurrent nested model) [61], we will draw and invite a purposive sub-sample from the overall pool of study participants at the end of Q2 to participate in this study component. We will aim to recruit 25-30 participants. Data will be collected using semi-structured individual interviews conducted by trained research team members in person or via Zoom. The interview will last about 1 hour, and participants will be offered a $40 gift card stipend during the enrollment process to thank them for their time and involvement. The interviews will be audio-recorded, transcribed verbatim, and entered in NVIVO 12 software for data organization and preparation for analysis.

Qualitative descriptive (QD) methodology is an appropriate approach for qualitative research aimed at generating information to refine interventions in everyday terms [60]. Aligned with QD methods [60], qualitative content analysis (QCA) will be conducted to summarize the content of the data [62, 63].

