**Methods:**

A pragmatic stepped-wedge cluster-randomized trial, where daily supportive text messages (Text4Support) and mental health peer support are the interventions, will be employed. We anticipate recruiting 10,000 participants at the point of their discharge from 9 acute care psychiatry sites and day hospitals across four cities in Alberta. The primary outcome measure will be the number of psychiatric readmissions within 30 days of discharge. We will also evaluate implementation outcomes such as reach, acceptability, fidelity, and sustainability. Our study will be guided by the Consolidated Framework for Implementation Research, and the Reach-Effectiveness-Adoption-Implementation-Maintenance framework. Data will be extracted from administrative data, surveys, and qualitative methods. Quantitative data will be analysed using machine learning. Qualitative interviews will be transcribed and analyzed thematically using both inductive and deductive approaches.

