### Study design

A pragmatic stepped-wedge cluster-randomized approach will be applied, providing Text4Support and Peer Support Service (PSS) to 10,000 participants recruited across 9 acute care sites and day hospitals across Alberta as the clustered unit of randomization (Fig. 1). The design reconciles constraints under which policy makers and service managers operate with the need for rigorous scientific evaluations. In a stepped-wedge study, the design is extended so every cluster provides pre-post observations, and switches from control to intervention exposure but not at the same time-point [42].

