**Fig. 1 Fig1:**
[figure not shown]
Number of new and total recruits expected in each cluster and period

The design is a preferable study design when:Evidence supports the intervention (e.g., known to be effective at individual level but uncertain about policy level), or there is resistance to parallel designs in which only half of the clusters receive the intervention.The intervention is a service delivery or policy change that can be implemented with the primary outcome, or at least some important outcomes available from routinely collected data (e.g., reduced readmission rates, acute care cost and no- show rates, routinely collected by AHS and primary study outcomes).The intra-cluster correlation is anticipated as high or cluster sizes large, so a cross-sectional stepped-wedge design is likely more efficient than a parallel cluster design.

This design has been successfully implemented with complex programs and change management involving large-scale programs in many countries [43, 44]. The study also adheres to checklists from the EQUATOR network ([45–47] (see Additional files 1 and 2).

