### Sample size considerations

We anticipate a reaching a target sample of 10,000. This figure is about 50% of expected psychiatric discharges, based on the 2018 administrative data (*n* = 20,747) [48]. We decided not to present detailed power analysis for sample size, which is controversial for stepped-wedge design approaches [49]. Further, our study is a pragmatic trial aiming to cause change in real-world conditions, rather than an explanatory trial which aims to study under ideal conditions. Thus, our approach is guided by the Pragmatic-Explanatory Continuum Indicator Summary 2 (PRECIS-2) toolkit with which we aim to align with the higher scores in pragmatism [50].

With our intended 5 randomized clusters and targeted overall project clinical population sample size of 10,000 (including accounting conservatively for 20% patient dropout and 10% dropout for PSWs), we are confident that our sample sizes are more than adequate as we expect at least medium-effect sizes, consistent with our prior results with supportive text messaging programs in Alberta [51].

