### Anticipated risks and limitations

Generally, this intervention portends little risk to participants, health workers, or the general public. Some participants may view this intervention as a replacement for outpatient or community face to face counseling post-discharge from acute care. However, this risk is neither supported by evidence from the literature or knowledge from implementing our predecessor program, the Text4Mood. Despite this, the PSS component of the Text4Support intervention will further eliminate the likelihood of this effect.

PSW burn-out is also a potential risk. To mitigate this risk, each PSW will be assigned a mental health therapist who will provide support and mentorship. Further, psychiatrists will be available to help where needed.

The ongoing COVID-19 pandemic and associated factors may pose risks to participants, researchers, and project implementation. To mitigate this, we will adhere strictly to the University of Alberta’s revised ethics guidelines for COVID-19 as well as the regularly updated guidelines and policies from the national and provincial authorities. Further, applying a pragmatic study design along with implementation science strategies and tools will help navigate the complex evolving study context caused by the pandemic’s other temporal trends. Operational level changes will be documented carefully, guided by RE-AIM and the Pragmatic-Explanatory Continuum Indicator Summary 2 (PRECIS-2) toolkit [50].

We expect the results for the primary, secondary, and exploratory outcome measures to be available within 3 years of project commencement. It is expected that the results will shed further light on the feasibility of using supportive text message combined with peer support interventions in long-term care for discharged psychiatric inpatients in Alberta. The anticipated outcome of the Text4Support & Peer Support project is illustrated in the logic model attached (Details in Fig. 2).

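### The only effectiveness contrast stated for the primary outcome, exposed versus unexposed periods, is confounded with calendar time in a stepped wedge if it is carried out as written

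*Protocol article*

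**What the plan says.** The abstract sets the primary outcome: "The primary outcome measure will be the number of psychiatric readmissions within 30 days of discharge". Under Study design, every cluster "switches from control to intervention exposure but not at the same time-point". Under Data analysis, the effectiveness comparison for the primary outcome is that the "distribution of primary outcomes data across unexposed observation periods will be compared with the exposed observation periods"; characteristics of individuals and clusters are to be summarised by exposure status so that imbalance can be considered.

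The regression and machine-learning models in the same section predict who is readmitted within 30 days. They do not estimate the effect of the intervention. The cost-utility paragraph describes "comparing resource use and health outcomes (health-related quality of life) for intervention and usual care cohorts" and controls for participant cohort characteristics, but mentions neither period nor cluster.

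Anticipated risks and limitations acknowledges temporal trends linked to the pandemic and says that the pragmatic design, with implementation strategies and tools, "will help navigate the complex evolving study context caused by" them. Among the conditions favouring the design, the article lists "The intra-cluster correlation is anticipated as high or cluster sizes large".

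The number of clusters is given in two ways. Study design has "9 acute care sites and day hospitals across Alberta as the clustered unit of randomization"; Sample size considerations has "With our intended 5 randomized clusters and targeted overall project clinical population sample size of 10,000".

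**The concern.** All clusters start unexposed and end exposed, so exposed versus unexposed is also late versus early. A comparison that does not hold calendar period fixed cannot separate the intervention from whatever else changed. A falling readmission rate would be credited to the programme, and a rising one would hide a real benefit. Recruitment starts in February 2022, monitoring runs over years 1 to 3, and the article itself expects temporal change.

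The safeguard is put in the wrong place. Pragmatism and careful documentation do not remove a secular trend from an effect estimate; a period term in the analysis does.

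Clustering is a second and separate matter. Early-crossing clusters supply most of the exposed data and late-crossing clusters most of the unexposed data. Under a randomised order this averages out, but with so few clusters it adds variance that a standard error ignoring clusters would miss.

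**Working it through.** The article gives no 30-day rate, intra-cluster correlation (ICC), alpha or power calculation, and Fig. 1 is not shown. There is therefore no figure of its own to reproduce, and what follows is an illustration.

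**Inputs from the article:** 10,000 participants; 5 randomised clusters (Sample size considerations); an expected reduction of 10-25% (Study aim).

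**Assumed:** 6 periods with one cluster crossing at each step, equal cells, 30-day rate 8% (the only rate given is a 90-day rate of up to 14.0%), two-sided 0.05, trend of 1 pp per year, true effect zero.

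**1. Time gap.** There are 15 exposed and 15 unexposed cells.
- Mean period, exposed: 70/15 = 4.67
- Mean period, unexposed: 35/15 = 2.33
- Gap: 2.33 periods

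**2. False difference from trend alone** (gap × period length × 1 pp per year).
- Quarterly steps: 2.33 × 0.25 = 0.58 pp
- Half-year steps: 2.33 × 0.5 = 1.17 pp
- Hoped-for effect: 10-25% of 8% = 0.8 to 2.0 pp

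**3. Rejection rate of an unadjusted test.** Standard error = √(2 × 0.08 × 0.92 / 5,000) = 0.54 pp.
- 0.58/0.54 gives a shift of 1.08 standard errors and rejection in about 19% of trials.
- 1.17/0.54 gives a shift of 2.15 standard errors and rejection in about 58%.

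**4. Clustering, no trend.** Net weights of the first to last cluster are (6 − 2k)/15 for k = 1 to 5, that is +0.27, +0.13, 0, −0.13, −0.27. They sum to zero and their squares sum to 0.178. The added variance is ICC × 0.0736 × 0.178.
- ICC 0.01: true SD 1.27 pp, type I error about 40%
- ICC 0.001: true SD 0.65 pp, type I error about 10%

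**5. With cluster and period terms.** After both sets of means are removed from the exposure indicator, its residual sum of squares is 15 − 9.17 − 11 + 7.5 = 2.33. With 333 participants per cell, the standard error is √(0.0736 / (333 × 2.33)) = 0.97 pp.

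A simulation at a 10% starting rate used 4,000 runs per scenario, relative falls of 0, 2% or 5% per period, and ICC of 0, 0.005 or 0.01. With cluster and period fixed effects, the mean estimate was about zero and rejection was 4.5-5.4% in all nine scenarios. With a 5% fall, the unadjusted test rejected in 46-56% of runs. The simulation had no cluster-by-period variation, so it is a favourable case for the adjusted model.

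**6. If 9 sites are the clusters** (10 periods, one crossing per step).
- Mean periods are 330/45 = 7.33 exposed and 3.67 unexposed, a gap of 3.67 periods.
- Over the same 18 months as six quarters, the false difference is 1.5 × 3.67/10 = 0.55 pp, against 0.58 pp.
- Squared weights, (10 − 2k)/45 for k = 1 to 9, sum to 240/2,025 = 0.119. Type I error at ICC 0.01 is about 32%.

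**The case against.** The strongest reply is that the sentence does not say the periods will be pooled or left unadjusted. It names no test or standard error, and a model with period and cluster terms also compares exposed with unexposed periods. An analysis plan that is not shown may contain such a model, and an article may leave that detail to it. A reader might infer that the trial has committed itself to an invalid pooled test; the text does not go that far. What remains is that the article fixes a contrast in words that are wrong for the design unless time is held constant, and assigns temporal trends to something that cannot remove them.

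A reader might also infer that differences between sites bias the estimate. Under a randomised crossing order they do not; they inflate type I error, and only if the standard error ignores clustering. The article does contemplate cluster imbalance, though only by summarising it.

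The figures are open to challenge too. Six half-year periods take 36 months, whereas the final analysis is set at the end of Q2 of year 3, about month 30 if quarters run from project start. Six periods within 30 months would last 5 months each and give 2.33 × 5/12 = 0.97 pp. The 1.17 pp and 58% are therefore an upper case. The quarterly 0.58 pp lies below the smallest hoped-for effect, but it is still 0.58/0.8 = 73% of it. A 5% relative fall per period amounts to 23% over five steps (1 − 0.95⁵), which nothing in the article supports. The trend, rate and ICC are all assumptions.

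**Conclusion.** The point holds against the comparison as stated. Followed literally, it confounds the effect on 30-day readmission with calendar time. The direction needs no assumed figure, because exposed time is later in any standard stepped wedge. The size does: about 0.6 pp of false difference per 1 pp per year of trend with quarterly steps, and up to about 1.2 pp with half-year steps, against 0.8 to 2.0 pp hoped for, assuming 5 clusters, 6 equal periods and an 8% rate. Counting 9 clusters changes the trend figure little.

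The inflation of type I error from clustering is conditional on clustering being ignored, which the article neither says nor excludes, and its size depends on an ICC that is not given. Since this concerns the primary estimate and the correction is cheap, it should be made in the protocol text and confirmed in the analysis plan.

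**What to change.** State under Data analysis that:
- the primary effect is estimated from a model with calendar period as a fixed effect and randomised cluster as a fixed or random effect;
- exposure is set by the cluster's condition on the participant's index discharge date;
- inference suits few clusters, for example permutation over the randomised order;
- the exposed-versus-unexposed comparison is descriptive only.

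Carry period and cluster terms into the cost-utility regression. In the section on risks, refer temporal trends to this model. Reconcile the two cluster counts, because the cluster term and any permutation depend on which unit is randomised. The exact model is a matter of choice: with about five clusters, variance components are poorly estimated, so fixed cluster effects are a reasonable option.

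The cost is wording and slightly more analysis, with no change to design or data collection. The standard error rises to about 1.0 pp from 0.54 pp under the assumptions above, and further if cluster-by-period variation is present. The precision is then less favourable than the unadjusted contrast suggests.

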### Components of the innovation

Peer support is valued in recovery-oriented models [15] of mental illness and increasingly implemented [16]. Evidence indicates positive effects, including lower inpatient service use, better relationships with providers and increased engagement. Peer Support Workers (PSWs) who are in recovery and have lived experience with mental illness will play central roles in this study, including delivering some of the interventions proposed. PSW activities will include supportive face-to-face visits, interactive phone calls/texts/zoom meetings with patients, advocacy, connecting patients with community resources, and experiential sharing. PSWs will be actively engaged through all provincial practice councils and are already embedded within many Alberta AMH programs. Evidence also shows that providing peer support to others may also benefit the PSWs by enhancing their own feelings of competence and personal value [17–22].Text4Support will be provided through ResilienceNHope, which is an online application site (https://application.resiliencenhope.com/). It is a low-cost, evidence-based, supportive text messaging program which will be coupled with or without mental health peer support services to reduce the psychological treatment and support gap for study participants who have been discharged from acute psychiatry care into community. Starting a day after enrolment, intervention-group participants will receive daily unidirectional (no-reply) supportive text messages. The text messages will be written by cognitive behavior therapists in partnership with individuals with lived experience of mental illness. The Text4Support program was developed based on knowledge from randomized controlled trials conducted in Ireland [23, 24] and Alberta [13, 25]. The program is also based on knowledge gained from the highly successful award winning Text4Mood program in Alberta’s North Zone which improved the psychological treatment gap and was effective [26] and scalable (i.e., > 10,000 recipients within 6 months). The Text4Hope program was launched in Alberta during the COVID-19 pandemic which was also effective and scalable (> 48,000 subscribers within 3 months) [27–37]. Text4Support provides CBT-based and diagnosis-specific daily supportive text messages for 6 months. Some examples of the text messages are:What lies behind you and what lies before you are tiny matters compared to what lies within you. Have faith in yourself, and success can be yours.There are 2 days in the week we should not worry about, yesterday and tomorrow. That leaves today. Live for today.Stumbling blocks can become steppingstones to a better life. You can turn adversities into opportunities. Don’t be discouraged by today’s problems.Letting go of resentment is a gift you give yourself. It will ease your journey immeasurably. Make peace with everyone, and happiness will be yours.

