### Participant recruitment

Individuals who have been diagnosed with a mental illness, are ready for discharge from an inpatient psychiatry unit that is part of the study, are 18 to 65 years of age, have a mobile device, can read English text messages, and can provide informed written consent will be eligible for the study. Recruitment will commence in February 2022 and will be done by the research team with physicians and other providers at the various sites. Participants should have a mobile device capable of receiving text messages. Participants will be ineligible if they know they will be based out of town during the 12-month follow-up period.

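### Individual consent in an apparently open stepped-wedge trial, with the unexposed population undefined and selection only described, leaves the primary comparison open to selection bias

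*Protocol article*

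**What the plan says.** All references are to the protocol article.

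- **Randomisation.** Study design names "9 acute care sites and day hospitals across Alberta as the clustered unit of randomization". Each cluster "switches from control to intervention exposure but not at the same time-point".
- **Entry.** Under Participant recruitment, patients who meet the other criteria (age 18 to 65, a mobile device, ability to read English texts) and who "can provide informed written consent will be eligible for the study". Recruitment "will be done by the research team with physicians and other providers at the various sites". Blinding of recruiters and concealment of switch dates are not mentioned.
- **Start of intervention.** Components of the innovation: "Starting a day after enrolment, intervention-group participants will receive daily unidirectional (no-reply) supportive text messages".
- **Primary comparison.** Data analysis takes the primary outcome from administrative data and compares unexposed with exposed periods. On selection it adds: "Characteristics of individuals/clusters will be summarized by exposure status to allow consideration of selection biases and lack of balance". A commitment to control for cohort differences appears later in that section, but for the cost-utility evaluation.
- **Who is unexposed.** Study design speaks of "providing Text4Support and Peer Support Service (PSS) to 10,000 participants", which read literally leaves no recruited controls. Components of the innovation refers to an intervention group, and the cost-utility text in Data analysis refers to a usual care cohort. Both imply recruited controls.
- **Denominator.** Table 1 defines Reach as "The proportion of target population who receive the daily supportive/reminder text message and peer support interventions across Alberta".

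**The concern.** Randomising clusters balances, in expectation and allowing for time, everyone discharged from them. It does not balance the subset who agree to join once the condition on offer is known. Staff who enrol patients for texts that begin the next day, or for no texts, very probably know which condition applies. Who is approached and who accepts may therefore change when the cluster switches.

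The article recognises selection bias as a possibility, but for the primary comparison it states only a description of characteristics. Description can reveal a measured imbalance. It cannot remove it, and it says nothing about unmeasured differences.

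The uncertainty over the unexposed set matters because the two readings carry different biases. With recruited controls, only differential consent or recruiter selection operates. With unselected administrative records as controls, the eligibility criteria and consent itself also separate the groups. At stake is whether a difference in 30-day readmission can be attributed to the intervention.

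**Working it through.** **Inputs from the article.** Target sample 10,000 and 20,747 discharges in 2018 (Sample size considerations); expected reduction 10–25% (Study aim). No 30-day readmission rate is given, so the work is done in ratios where possible.

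**1. The article's own figure.** 10,000 / 20,747 = 48.2%, consistent with its statement of about 50%. If recruitment ran for two years at the same volume (assumption), the share would be 10,000 / 41,494 = 24.1%.

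**2. Reading A: exposed = enrolled participants, unexposed = all discharges, no true effect.** Let s be the enrolled share and r the risk in non-enrolled patients divided by the risk in enrolled patients. Then

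spurious RR = 1 / [s + (1 − s) r], so r = (1/RR − s) / (1 − s).

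| Spurious reduction | s = 0.482 | s = 0.241 (assumed) |
|---|---|---|
| 10% (RR 0.90) | (1.111 − 0.482)/0.518 = 1.21 | (1.111 − 0.241)/0.759 = 1.15 |
| 25% (RR 0.75) | (1.333 − 0.482)/0.518 = 1.64 | (1.333 − 0.241)/0.759 = 1.44 |

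**3. Reading B: both sets are recruited, no true effect.** Assume for illustration that high-risk patients carry 3 times the risk of others and make up 40% of unexposed recruits. Mean relative risk is 0.6 + 0.4 × 3 = 1.8. With share x of high-risk patients among exposed recruits, the mean is 1 + 2x.

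- Spurious 10% reduction: 1 + 2x = 0.90 × 1.8 = 1.62, so x = 31%.
- Spurious 25% reduction: 1 + 2x = 0.75 × 1.8 = 1.35, so x = 17.5%.
- Spurious 10% increase: 1 + 2x = 1.10 × 1.8 = 1.98, so x = 49%.

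A shift of 9 percentage points in case mix, in either direction, thus moves the result by 10%.

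**4. What an all-discharge analysis would cost.** If only participants benefit, the reduction across all discharges is s × (1 − RR).

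- s = 0.482: 4.8% to 12.0%.
- s = 0.241: 2.4% to 6.0%.

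Upper-bound power follows, assuming two-sided 5% alpha, an equal split, no allowance for clustering or time, and 30-day rates of 5% / 8% / 10%:

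| True RR in participants | 5,000 v 5,000 participants | 10,373 v 10,373 discharges, diluted at s = 0.482 |
|---|---|---|
| 0.75 | 86 / 97 / 99% | 54 / 75 / 85% |
| 0.90 | 22 / 33 / 40% | 12 / 18 / 22% |

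**The case against.** Much can be said on the other side.

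- **Knowledge of the condition is inferred.** A reader might take it as stated that consent follows disclosure of the cluster's condition. The article does not say when sites learn their switch date. The inference is strong in an apparently open design, but it remains an inference.
- **Adjustment may be planned elsewhere.** A baseline description does not exclude a covariate-adjusted model, and a statistical analysis plan may contain one. The absence of model detail here is therefore not the finding. What stands is that the article itself leaves the unexposed population ambiguous, and that adjustment would not remove unmeasured selection.
- **The 10,000 may be loose wording.** The same section describes every cluster moving from control to intervention, and Fig. 1, which is not reproduced in the text available, may give the split. The passages still need to be reconciled.
- **48% is not an uptake rate.** It sets a whole-project target against one year of discharges, which are not stated to be limited to study sites or to ages 18–65. A reader might infer that half of the patients approached will join; that does not follow.
- **Phone and English criteria do not always separate the groups.** If controls are recruited, these criteria apply equally to both sets. They matter only if controls are unselected records.
- **The direction is not documented.** A reader might infer that joiners are lower risk and that the bias favours the intervention. Nothing in the article establishes this. Peer support is to be offered to those most at risk of readmission, so recruitment could lean the other way.
- **A null all-discharge result would be hard to interpret**, given the dilution. This stands, and it is why that analysis should be supplementary.

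**Conclusion.** The concern holds in a conditional form. Individual consent through site staff in an apparently open design exposes the primary comparison to selection that a table cannot repair, and the article does not settle who makes up the unexposed periods.

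If controls are recruited, the bias may go either way and its size cannot be derived from the article; the case-mix example shows only that a moderate shift is enough. If controls are all discharges, a risk ratio of 1.21 to 1.64 between non-enrolled and enrolled patients would reproduce the whole expected range, assuming a 48.2% enrolled share, and smaller ratios would do so at a smaller share.

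The documents do not support a single figure for the bias, such as a spurious fall of about a quarter. That would need assumed absolute risks, unselected controls and a known direction all at once.

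**What to change.** 1. **Reconcile the text.** Bring Study design into line with Components of the innovation and the cost-utility text in Data analysis. State whether unexposed periods contain recruited participants or all discharges, and how many of the 10,000 are expected under each condition.
2. **Adjust the recruited-participant analysis** for baseline risk. Data analysis already lists prior-year readmissions and diagnosis among the variables for its prediction models.
3. **Add a pre-specified supplementary analysis** of 30-day readmission in all discharges aged 18–65 from participating units. Classify each by the cluster's condition on the discharge date, regardless of consent or uptake, with cluster and period terms. Because records may not show phone ownership, English reading or planned absence, the set should rest on criteria that they do show.

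**Cost.** A wider extraction of routine data, possibly with ethics approval for records of patients who did not consent. Reach already calls for a target-population denominator, although that alone does not establish access to patient-level outcomes. The analysis does nothing for the survey outcomes, and it dilutes the effect in proportion to actual reach. Report it beside the participant analysis, with the achieved reach, and not in its place.
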